### Participants

#### Adolescents and Their Parents

All adolescents in our study will be boys, as girls are not referred to the two JJIs concerned. The boys will be between 12 and 18 years old at the time of placement. All youth placed in a FC group will be offered FC, but not all of them will be included in our study. An adolescent will be excluded (1) if his stay in the short-term stay group lasts less than 14 days (we need a minimum of two weeks to complete all assessments for the study); (2) if he does not have a parent or a parent figure; (3) if he already participated in our study during a previous stay; (4) if he does not understand Dutch; (5) if he and his parents refuse to take part in the assessments; (6) if he is already sentenced by the juvenile judge to a so-called PIJ order (Placement in an Institution for Juveniles for mandatory treatment) which implies long-term detention with treatment, or (7) if he is temporarily transferred from another institution.

As our assessments will be part of the Routine Outcome Monitoring (ROM) and of the standard screening and diagnostic procedures, psychologists can withhold the adolescent or his family from assessments, for example in case of severe psychiatric disorders. Reasons for excluding participants from the study will be noted. Consequently, we will first consult psychologists before approaching adolescents and their parents for the interviews. In general, following the psychologists’ advice, we will not approach them in case of an alleged sex crime or when severe psychiatric disorders such as mental retardation, psychosis, autism, or acute suicidal behaviors are present.

Because the questionnaires in the quantitative part of our study are embedded in the standard procedures in the institutions, no incentives will be used for youth and parents. For the interviews, however, youths will receive extra television time in their rooms and parents will receive a small incentive such as a mug filled with chocolates and a personal thank you note.

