### Setting

This study will be carried out in two JJIs in the Netherlands. A juvenile judge can refer an adolescent to a short-term stay group in a JJI for pre-trial detention. Depending on the interim ruling of the juvenile judge, the time spent in pre-trial detention can last for a few days up to a maximum of customarily 90 days. As a rule, the juvenile judge refers the adolescent to a JJI close to the home of the youth. The JJI’s secretarial office monitors a group’s capacity and decides on which group the adolescent is placed.

One of the JJIs has three short-term stay groups. The management of this institution chose two of these groups for a step-by-step implementation of the FC program, while the third group will continue to offer UC. Of the two short-term stay groups in the other JJI, the management chose one to offer FC, and the other UC. The managements of the two JJIs based their choices for the groups starting with the implementation of FC on pragmatic considerations. Because the JJIs are required to fill free slots in the living groups if new adolescents are referred to the institutions, the assignment of adolescents to groups is not dependent on characteristics of youths and is therefore without bias.

Each team of about 10 group workers is headed by a team leader and collaborates with a psychologist or pedagogue (hereafter jointly referred to as psychologist), who is responsible for coordinating the treatment the adolescent will receive.

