### Recruitment and Sample Size

Adolescents and parents are informed of the JJI’s research activities by a flyer in the information leaflets from the JJI. The flyer informs that the data will be used anonymously in research studies and that parents can address their questions concerning these activities to their child’s mentor (one of the group workers) or to the psychologist.

The JJIs in the Netherlands jointly apply ROM and standard screening and diagnostic procedures for detained adolescents and their parents. As our assessments will be embedded in these procedures, the quantitative part of our study will use data collected in the two participating JJIs by these means. Recruitment of adolescents and their parents in the quantitative part of our study will last 21 months, including the pilot stage of 7 months. Based on records from 2011, the year prior to the pilot stage, we estimate that in 21 months, 300 adolescents will be placed in the groups concerned. Taking into account the exclusion criteria, we expect to recruit 160 adolescents and parents for the present study. Based on previous research, this number suffices for establishing statistically significant differences on quantitative measures between the two conditions [9].

As for qualitative studies, 10 interviews are generally sufficient to achieve saturation (ie, the point where additional interviews do not yield new essential information regarding the research question) [32]. Once an eligible adolescent is placed in a short-term stay group (either FC or UC), he and his parents will be invited to participate in the qualitative part of the study. If they are willing to participate, an appointment will be made for the interview. We will interview 10 boys (5 aged < 16 years and 5 aged > 16 years) in each JJI (N=20). We will also interview 20 parents (10 in in each JJI, 10 fathers and 10 mothers, 10 with a detained child aged < 16 years, and 10 with a detained child aged > 16 years). Finally, we will interview 20 FC group workers and 20 UC group workers.

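### The re-admission exclusion is keyed to earlier study participation, not earlier FC exposure, so a boy with a non-included FC stay can later be analysed as UC

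*Protocol article*

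**What the plan says.** The section Adolescents and Their Parents separates receiving FC from being studied: "All youth placed in a FC group will be offered FC, but not all of them will be included in our study". Its only rule on repeat stays is "3) if he already participated in our study during a previous stay".

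Three routes lead to an FC stay that is not included:
- a short stay: "if his stay in the short-term stay group lasts less than 14 days";
- refusal: "5) if he and his parents refuse to take part in the assessments";
- a clinical decision: "psychologists can withhold the adolescent or his family from assessments".

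On the length of stay, the Setting section says "the time spent in pre-trial detention can last for a few days up to a maximum of customarily 90 days". On placement it says "The JJI’s secretarial office monitors a group’s capacity and decides on which group the adolescent is placed", and adds that free slots must be filled and that assignment does not depend on the boy's characteristics. Each of the two JJIs runs both conditions: two FC groups and one UC group in one, one of each in the other.

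Under Recruitment and Sample Size, "we estimate that in 21 months, 300 adolescents will be placed in the groups concerned", of whom 160 are expected to be recruited.

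**The concern.** An exclusion for repeat stays should keep families who have already had the intervention out of the comparator. This one works only if every FC-exposed boy was also a participant, and the same section says that is not so. A boy who was in an FC group but not in the study meets no exclusion on that account when he returns. If the free place is then in a UC group, he is analysed as UC.

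Nothing else in the article closes the gap. The contamination safeguard in the Staff section concerns group workers only and is worded as a preference. The covariate rule under Quantitative Analyses covers demographic factors that differ, and the JJI if necessary. Earlier FC is not named.

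Carry-over is plausible. The Family-Centered Care section treats the first phase of detention as the time to build an alliance with parents, and lets family therapy begun in detention continue after discharge. If it occurs, some UC families already carry part of the effect being tested on involvement, motivation and satisfaction. The same gap admits boys to the FC arm on a second exposure, with a baseline that may already be altered.

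**Working it through.** **The plan's own figure.** The 160 cannot be reproduced as a sample size, because the article gives no alpha, power, effect size or standard deviation. It is used here only as the expected number included.

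**Inputs from the article**
- Placed: 300. Included: 160. Inclusion rate: 160/300 = 0.533.
- Groups: 3 FC and 2 UC.

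**Assumptions**
- Placements divide 3:2 by number of groups.
- A share r of non-included boys returns within the window. No rate is given, so r = 5%, 10% and 20% are shown.
- A returning boy is placed in UC with probability 2/5 and is included at the plan's overall rate.

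**Step 1: boys exposed to FC but not included**
- 300 - 160 = 140
- 140 x 3/5 = 84

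**Step 2: expected arms**
- 160 x 3/5 = 96 FC
- 160 x 2/5 = 64 UC

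**Step 3: UC boys with earlier FC** = 84 x r x 2/5 x 160/300

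| r | UC boys with earlier FC | Share of 64 |
|---|---|---|
| 5% | 0.9 | 1.4% |
| 10% | 1.8 | 2.8% |
| 20% | 3.6 | 5.6% |

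**Step 4: FC boys on a second FC exposure** = 84 x r x 3/5 x 160/300
- r = 10%: 2.7 of 96 (2.8%)
- r = 20%: 5.4 of 96 (5.6%)

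**Step 5: effect on a between-group test.** Let c be the contaminated share of UC. Under complete carry-over a true standardised difference d shrinks to d(1 - c); under half carry-over, to d(1 - c/2). The reference case is an assumed two-sided alpha of 0.05, 96 versus 64 boys and d = 0.454, which gives 80.3% power without contamination.

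| r | Power, complete carry-over | Power, half carry-over |
|---|---|---|
| 10% | 78.1% | 79.2% |
| 20% | 75.7% | 78.1% |

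No multiplicity correction is applied here, although the plan promises one.

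**The case against.** The case on the other side is mostly about size, and much of it stands.

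- **Frequency.** A reader might infer that crossover is to be expected because free slots decide placement. The article does not support that: it gives no re-admission rate. It supports only that crossover can happen and that nothing prevents it.
- **A larger share.** A reader might also reach 5-10% of the UC arm. That is 84 x 0.10 x 0.4 = 3.4 to 84 x 0.20 x 0.4 = 6.7 of 64, and it requires every returning boy to be included. The plan expects 160 of 300.
- **The base of 140 is generous.** It contains boys with lasting reasons for exclusion (no parent figure, no Dutch, a PIJ order), and boys already barred by criterion (3). The 3/5 FC share may also be too high early on, since implementation is step by step in one JJI.
- **Short stays are the weakest route.** A stay under 14 days ends before the third-week meeting that FC stresses. UC on paper also includes weekly telephone contact and an invitation to the group, although the article says this is barely practised. Refusal and withholding matter more, because those stays could run to about 90 days.
- **Direction.** A bias towards no difference is not assured for every outcome. Visits depend partly on what current staff do. A family moving from FC to UC might rate UC lower by contrast, which would widen the satisfaction difference. Where the week-3 baseline enters the analysis, it may itself be shifted.
- **Partial cover.** A short questionnaire asks about past treatment, and reasons for exclusion are noted. Neither identifies an earlier FC stay by name. A fuller protocol might treat repeat stays in more detail, but the criterion as printed is explicit and is tied to participation.

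None of this removes the gap in the wording.

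**Conclusion.** The point holds as a gap in the eligibility rule whose effect is probably modest. Criterion (3) does not bar a boy with an earlier, non-included FC stay from entering as UC or from re-entering FC. At an assumed 10-20% re-admission, a 3:2 split and the plan's 160/300 inclusion rate, about 2 to 4 of 64 UC boys (3-6%) would have had FC before, and probably fewer because some exclusion reasons persist. Even with complete carry-over, reference power falls by only about 2 to 5 percentage points.

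Dilution of between-group differences is the likely effect. Its direction is uncertain for satisfaction and for analyses that use the week-3 baseline. The re-admission rate, the split, inclusion on return, alpha, effect size and degree of carry-over are all assumptions. The article does not support a claim of large or certain bias. The reason to act is that the comparator should not contain families who have already had the intervention, and that the check is cheap.

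**What to change.** Key criterion (3) to exposure and apply it alike in both arms: exclude from the FC-UC comparison any stay preceded by a stay in one of the five study groups since FC began, whether or not the boy took part then. Identify these stays from JJI placement records.

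The Discussion says data collection was completed in 2015. If enrolment is closed, flag these boys, report their number by arm, and repeat the FC-UC comparison without them in both arms as a sensitivity analysis.

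Do not exclude them from UC only. That would remove re-detained boys from one arm and keep them in the other, which could bias problem behavior and return home.

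**Cost.** One sentence and a look-up. Under the assumptions above, the boys lost number 140 x r x 160/300, which is 7.5 at r = 10% and 14.9 at r = 20%, of 160 in both arms together. Persistent exclusion reasons would lower this. With the 3:2 split kept, reference power after exclusion would be 78.4% or 76.4%, close to the power under complete carry-over. The gain is therefore a clean comparator, not power. As a sensitivity analysis the change costs the main analysis nothing.

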### Study Objectives and Research Questions

The overall aim of our study is to evaluate FC in the first two years after the first steps of its implementation in short-term stay groups in JJIs. The key question to be answered in the quantitative part in the second stage of the study is if FC has additional value compared to UC. We will test the following hypotheses comparing FC with UC during detention: (1) FC increases parents’ involvement with their detained child; (2) FC increases the motivation of the adolescent and his parents for accepting treatment and guidance by JJI staff and for taking part in family meetings; (3) FC adolescents show less problem behavior; (4) FC improves family interactions; (5) FC parents experience less parenting stress; (6) FC youth more often return to their families’ home upon discharge; (7) FC enhances adolescents’ and parents’ satisfaction with the JJI; (8) In FC groups, JJI staff members are more satisfied, feel more confident in their contact with parents, and more often incorporate the family perspective in their thinking.

Finally, we will study if parents who participate in family-centered activities, differ from parents who do not participate based on characteristics such as proximity to the JJI, age of their child, duration of his stay, and baseline outcomes in other demographics, family functioning, parenting stress, treatment motivation, and satisfaction.

The aim of the qualitative part of the study is to trace which factors influence parental involvement. We will interview adolescents, parents, and group workers from short-term stay groups based on the following research questions: (1) How do adolescents, parents, and group workers feel about the current involvement of parents in FC and UC? (2) What are the attitudes of FC and UC group workers towards working with parents? (3) What are the needs, wishes, and expectations of adolescents, parents, and group workers concerning FC?

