#### Parents’ Involvement During Their Child’s Detention

To examine to which extent parents are involved with their sons, we will record the number of visits by parents and the purpose of each visit to the JJI. Group workers, team leaders, and psychologists will note when they have had contact via telephone with the parents.

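### Refusing the questionnaires removes a boy from the whole study after family-centered care has begun, which can bias outcomes that need no questionnaire; size and direction are unknown

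*Protocol article*

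**What the plan says.** **Exposure and inclusion are separate.** Under Adolescents and Their Parents: "All youth placed in a FC group will be offered FC, but not all of them will be included in our study". The fifth of seven exclusion criteria there reads "5) if he and his parents refuse to take part in the assessments".

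**Withholding.** The same section says that "psychologists can withhold the adolescent or his family from assessments, for example in case of severe psychiatric disorders", and continues: "Reasons for excluding participants from the study will be noted". Under Setting, each group's team "collaborates with a psychologist or pedagogue (hereafter jointly referred to as psychologist), who is responsible for coordinating the treatment the adolescent will receive".

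**Timing.** Under Assessments, baseline is in the third week of detention. Under Family-Centered Care, the first phase of detention is described as the moment to win parents' engagement. Hypothesis 2 expects FC to raise the motivation of boys and parents to accept the institution's treatment and guidance.

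**Outcomes that need no family questionnaire.** Incidents come from daily reports and the institution's database, and cannabis results from that database. For parental involvement, "we will record the number of visits by parents and the purpose of each visit to the JJI", and staff note telephone contacts. Psychologists note the living situation after discharge on a separate form. These sources serve hypotheses 1, 3 and 6.

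**Participation question.** Under Study Objectives and Research Questions: "we will study if parents who participate in family-centered activities, differ from parents who do not participate". The listed characteristics include distance, the boy's age and length of stay, as well as baseline questionnaire scores.

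**Safeguards.** Reasons for exclusion are noted, and Quantitative Analyses promises a flowchart that shows them. Covariates are demographic factors that differ between groups and, if necessary, the institution.

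**The concern.** A family accepts or refuses the assessments after about two weeks in its program. During those weeks FC staff work on the parents' willingness to engage. If FC changes who refuses, the two analysed samples differ in composition even if the boys placed in the groups did not. The article's argument that placement does not depend on the boys' characteristics covers placement only. It gives no protection against a selection made later.

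For questionnaire outcomes some loss is unavoidable, because a family that refuses gives no scores. For incidents and cannabis, and for visits, telephone contacts and living situation where logged, the loss comes from the eligibility rule alone.

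At stake are the FC versus UC comparisons for hypotheses 1, 3 and 6. The participation comparison is affected too, because families who keep their distance from the institution are plausibly over-represented among refusers. For withholding, the worry is a discretionary decision by someone who knows which program the boy is in. The link to parental motivation is weaker there.

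**Working it through.** **1. What the article's own figures show.** Recruitment and Sample Size expects 300 placements and 160 recruited. 160/300 = 53.3% retained, so 140 (46.7%) are lost through all exclusion criteria together. The 160 cannot be rebuilt, because no loss per criterion is given. The share due to refusal or withholding is unknown.

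**2. Detectable effect, for scale.** There are three FC and two UC groups, so a split in proportion gives 160 × 3/5 = 96 and 160 × 2/5 = 64. Two-sided alpha 0.05 and 80% power are assumed:

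- SE = √(1/64 + 1/96) = 0.161 SD
- detectable difference = (1.960 + 0.842) × 0.161 = 0.45 SD (0.44 SD with 80 per group)

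**3. Bias if exclusion differs by group.** All inputs here are assumed. Motivation is standard normal, the least motivated share r is excluded, motivation correlates ρ with an outcome scored so that higher is better, and FC has no true effect. The mean motivation of those kept is m(r) = φ(z_r)/(1 − r), which gives m(0.1) = 0.195, m(0.2) = 0.350 and m(0.3) = 0.497. Then bias = ρ × [m(r_FC) − m(r_UC)].

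| Excluded FC / UC | Bias, ρ = 0.3 | Bias, ρ = 0.5 | Type I error, 96/64 |
|---|---|---|---|
| 10% / 10% | 0 | 0 | 5% |
| 10% / 20% | −0.05 SD | −0.08 SD | 6.0% / 7.7% |
| 20% / 30% | −0.04 SD | −0.07 SD | 5.9% / 7.4% |
| 10% / 30% | −0.09 SD | −0.15 SD | 8.7% / 15.5% |
| 30% / 10% | +0.09 SD | +0.15 SD | 8.7% / 15.5% |

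The sign depends on which group loses more families. Excluding strictly from the bottom of the motivation scale is a strong form of selection, so for a given r and ρ these values lie toward the high end.

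**4. What the joint condition does.** Assume 60% engaged families (1.5 visits per week) and 40% unengaged (0.5 per week), with no true effect. With nobody excluded, both groups average 0.6 × 1.5 + 0.4 × 0.5 = 1.10. Parents refuse in 10% of engaged families. In unengaged families they refuse in 50% under UC and 25% under FC.

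- *If the parents' refusal alone removed the boy:* UC (0.54 × 1.5 + 0.20 × 0.5)/0.74 = 1.23; FC (0.54 × 1.5 + 0.30 × 0.5)/0.84 = 1.14; gap −7%.
- *If both must refuse, with boys refusing independently in 20%:* joint refusal is 2% in engaged families, and 10% (UC) or 5% (FC) in unengaged ones. UC (0.588 × 1.5 + 0.36 × 0.5)/0.948 = 1.120; FC (0.588 × 1.5 + 0.38 × 0.5)/0.968 = 1.107; gap about −1%.

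The second calculation is the one that follows criterion 5. If boys and parents tend to refuse together, the gap lies between the two results.

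**5. Which records exist without the questionnaires.** The article describes incidents and cannabis tests as routine institutional data. Visits, telephone contacts and the discharge form are described as things the study or staff will record. Nothing says that they are kept for boys outside the study.

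**The case against.** The best defence is that the rule bites little. It requires refusal by the boy and his parents, so an unwilling parent alone does not remove him. The assessments are embedded in routine monitoring and standard screening, which gives no reason to expect much refusal or a large gap between groups. With equal refusal there is no between-group bias in the model above. Reasons are noted and a flowchart is promised, and outcome-specific analysis sets often belong in a document not shown here. All of this stands as a limit on size. It does not remove the point: the eligibility rule is itself stated, and the safeguards show the selection without correcting it.

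The defence also holds for part of the participation comparison. It concerns taking part in family activities, not in the study, and the article reports from the pilot that not every parent visited or attended, so the included sample will contain non-participants. Refusers could never supply most of the listed characteristics. Only distance, age and length of stay can be recovered.

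A reader might infer stronger claims that the document does not support:

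- That close to half the boys are lost to refusal: the 140 of 300 covers every criterion, including stays under 14 days, transfers and earlier participation.
- That withheld families certainly leave the whole study: this is only implied by the sentence after the withholding rule, and the one example given is severe psychiatric disorder, not low motivation.
- That every register outcome exists for every boy: only incidents and cannabis are plainly routine.

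**Conclusion.** The point holds in limited form. As written, criterion 5 selects the study sample after exposure, on behaviour plausibly tied to the engagement that FC tries to raise, and applies that selection to outcomes that do not need it. Withholding probably works the same way, at the discretion of a psychologist who knows the program.

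Neither size nor direction can be derived from the article. Under the assumptions shown, a difference of 10 to 20 percentage points in exclusion moves a register outcome by about 0.04 to 0.15 SD, and equal exclusion by nothing. Under the joint-refusal condition the visit illustration gives about 1%. It would be wrong to conclude that FC is shown at a disadvantage, or an advantage, since either can occur. Even with equal refusal, the participation comparison probably loses some of its least engaged families, by an amount that cannot be stated. That refusal tracks motivation is an inference, though one in line with the program's own rationale. The change is worth making because the rule is unnecessary for these outcomes and cheap to narrow.

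**What to change.** - Apply refusal and withholding per informant and per questionnaire only.
- Keep otherwise eligible boys, in the group where they were placed, for incidents and cannabis. Do the same for visits, telephone contacts and living situation where these logs exist for them. Leave out boys whose family objects to use of the records.
- Use this same set for the participation comparison on distance, age and length of stay.
- Report counts of refusal and of withholding separately for FC and UC, and state whether a withheld family leaves the study or only the assessments.

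**Cost.** Wording, and extraction from databases for incidents and cannabis. The analysis set becomes larger for register outcomes than for questionnaires and must be labelled so. Objections to record use must be checked and honoured, which matters for detained minors whose families declined the assessments. The Discussion says data collection ended in 2015, so visit, telephone and discharge logs that were not kept for non-assessed boys cannot be recreated. For those outcomes the remedy is then limited to reporting refusal and withholding by group and naming the selection as a limitation.
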